#### Inclusion and exclusion criteria

Families with existing in-patient coverage of SSP, having SSP cards, and currently residing within the intervention or control areas of selected UCs of ICT will be considered eligible for inclusion in the research study and the baseline survey. Families not yet registered as beneficiaries with SSP and married children of SSP card holders were excluded. The endline survey will also follow similar inclusion–exclusion criteria as the baseline, i.e., to be conducted on those beneficiaries who were enrolled for the research study in the intervention and control UCs and those who were refusals or migrated cases will be excluded from the endline survey. The eligibility of each beneficiary family will be re-verified before inclusion through the National Database and Registration Authority (NADRA) website and by sending a Computerized National Identity Card (CNIC) number to 8,500 via short message service (SMS).

#### Study duration

The total duration of this research study is 24 months, with the following phases:

6-month inception period.12 months research intervention period.A 3-4-month period is dedicated to endline evaluation.

##### The benefits package - modified essential package of health services (EPHS)

The intervention group will receive the outpatient EPHS developed for the primary health care level, including sexual and reproductive health (48, 49) at the selected facilities, which include 10 broad categories of essential services with mandatory services and some referral services.

A list of the broad categories of EPHS are as follows:

**Table tab1:** 

Reproductive Health, including modern contraceptives and post-abortion care	Childcare
Delivery Care (only low-risk BEmONC; otherwise, all referrals to higher-level facilities)	Adolescent health
Antenatal care	Infectious diseases
New-born care	Non-communicable diseases
Post-natal care	Basic tests and medicine (only approved for this study)

### Quantitative household surveys

Before initiating the intervention, a household-based baseline survey is proposed that will cover not only the study population but also a subset of the general population from the same catchment who do not have the provision of any public or private sector health insurance. Findings will explore and explain health-related expenses and payment mechanisms if practiced or that exist other than the fee for service paid through OOP by clients in the study catchment area. The baseline survey will assess the prevalence of study indicators, document socio-economic and demographic information, out-of-pocket health expenditure, and document KAP regarding existing inpatient coverage and access and uptake of health services. A household-based endline survey at the end of 12 months of the intervention will help assess study outcomes – the impact of the outpatient services model on knowledge, attitude, and practice regarding health insurance, access, and uptake of outpatient services at the PHC level, user satisfaction, treatment outcomes, OOP health expenditure and financial protection.

Study participants for baseline and end-line assessment across the intervention and comparison arm will be selected randomly from the list frame of the SSP. Using quantitative and qualitative techniques, data collection methods will include a population-based household survey, providers’ assessment, and specific qualitative inquiry during the intervention, routine services, client satisfaction, and monitoring (clinical quality assessment) data will be done similarly to a previous study using the same design (50).

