#### Study population and sample size

The target population will be divided into (a) demand-side and (b) supply-side.

*Demand Side:* The total sample size for this study is 1726 beneficiary families (Baseline and end-line: control and intervention). This has been calculated by assuming the overall prevalence of health outcomes to be 50% (conventional) at baseline and an anticipated 10-percentage point change because of the intervention; with 80% power and 0.05 significance level, the total estimated sample was 388 for each study arm. The estimated sample was adjusted for a design effect 2 to account for facility-level clustering and 10% missing data / non-response. Hence an overall sample size of 863 families in the intervention- and 863 families in the control- group will be required to test the study objectives. Families in each study arm will be selected randomly from the available list of SSP beneficiary families from four peri-urban Union Councils of Islamabad Capital Territory (ICT). The intervention group (*N* = 863) will receive modified EPHS interventions as OPD services, while the Control group (*N* = 863) will not receive OPD services. Enrolled families in the intervention group will be informed about the project, and regular follow-up of SSP outpatient services accessed will be undertaken.

*Supply Side:* GPs who are members of Marie Stopes Pakistan’s primary healthcare franchise network will be selected based on their service provision status within the UCs identified for research study implementation. Individual and facility assessments will be done to ascertain the capacity to provide quality OP services to clients. A training curriculum will be jointly developed by the MoNHSRC, SSP, MSS, and WHO and will be used to train the selected GPs on the modified EPHS services. Periodic quality assurance visits and a centralized data-collection management information system will be implemented.

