
The validity is often compromised in quasi-experimental designs; however, our study will use statistical techniques and control measures to strengthen its validity, such as developing a study protocol as a standardized way to conduct the study to prevent researcher, instrumentation, or testing biases. When everyone follows the specific procedures, you can be more confident that the results will be valid. We will carefully select the control facility and justify the choice of the control group, ensuring that the control group is comparable to the intervention group in terms of relevant characteristics. A matched pre-post design would have been a stronger study design to compare behaviors of the same sample, as it will allow controlling for unobserved confounders such as to help address selection bias issues, control baseline differences and improve group comparability. Through Difference-in-Differences (DiD) analysis, we will compare outcome changes between the intervention and control groups, accounting for pre-existing trends. This will help control external factors that may affect both groups similarly. We will conduct validity checks for balance in covariates between groups before and after matching or weighting procedures. We will also provide clear and transparent reporting of methods, measures, and results to enhance the credibility and replicability of the study. In addition, respondents may have faced difficulties in answering questions or recall bias that captured information about their past experiences, such as information provided by the service provider about side effects at the time of method uptake, decision making and source of referral to the health facility or where the contraceptive method was adopted, exact time and discontinuation of method etc. Hence, whenever possible, we will try to supplement self-reported data with objective measures to validate the information provided by participants. Or to use standardized instruments and validated questionnaires to enhance the reliability of data collection.

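### The protocol is inconsistent on whether the endline re-interviews the enrolled families or may draw a new sample, and the DiD precision depends on the answer

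*Protocol article*

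**What the plan says.** Three sections of the protocol article describe who is interviewed at endline.

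- Inclusion and exclusion criteria says the endline is "to be conducted on those beneficiaries who were enrolled for the research study in the intervention and control UCs", and that "those who were refusals or migrated cases will be excluded from the endline survey".
- Quantitative household surveys says "Study participants for baseline and end-line assessment across the intervention and comparison arm will be selected randomly from the list frame of the SSP". It does not restrict the endline to enrolled families and does not say how many times the selection is made.
- Possible limitations and strengths says "A matched pre-post design would have been a stronger study design to compare behaviors of the same sample". The conditional presents this as a design that was not adopted.

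Two other sections bear on the reading. Study population and sample size gives a single total: "The total sample size for this study is 1726 beneficiary families (Baseline and end-line: control and intervention". Ethics and dissemination gives each participant a unique identifier, built from home address and allocated facility, to be used on all study forms.

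The main quantitative analysis is DiD (Data analysis). The outpatient benefit goes only to families enrolled and allocated to a facility (Capitation-based provider payment mechanism), which is the 863 families of the intervention arm.

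**The concern.** The eligibility text describes a closed cohort. Excluding families that have migrated makes sense only if known families are being followed. The limitations text implies that the same families are not compared. These two conflict however the survey section is read, and the survey section is itself open to both readings.

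Two things depend on the answer. The first is precision: the DiD standard error differs between paired and independent waves. The second arises only if the survey section were carried out as a new, unrestricted draw. The intervention-arm endline would then include listed families who were never offered outpatient cover, and the contrast would no longer be an effect on benefit holders.

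An external party runs both surveys. Who is interviewed is a field decision, and analysis cannot repair it afterwards.

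**Working it through.** **1. Reproducing the plan's sample size.** Inputs from Study population and sample size: a 50% prevalence before the intervention; a 10-point effect; "with 80% power and 0.05 significance level, the total estimated sample was 388 for each study arm"; design effect 2; 10% non-response. Sidedness is not stated; two-sided reproduces the figure. With p1 = 0.50, p2 = 0.60 and mean 0.55:

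n = [1.96·√(2·0.55·0.45) + 0.8416·√(0.25 + 0.24)]² / 0.10² = (1.379 + 0.589)² / 0.01 ≈ 387.3, rounded up to 388.

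388 × 2 = 776; 776 / 0.90 = 862.2, rounded up to 863 per arm; 2 × 863 = 1726. The stated figures reproduce. The formula is a two-group comparison at one time point, so 863 families carry the information of 388 independent families per arm per wave.

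**2. Reading the passages together.**

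- Eligibility text: endline limited to enrolled families, which is a cohort.
- Survey text: compatible with one draw surveyed twice, or with a second draw.
- Limitations text: same-sample comparison forgone.
- Single total of 1726 and a common identifier: both favour a cohort, but neither states that baseline and endline are linked.

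**3. DiD precision, with no dilution.** Assume 388 effective families per arm at each wave, control at 50% in both waves, intervention moving from 50% to 60%, and baseline–endline correlation ρ in both arms (not given in the document):

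Var(DiD) = [(0.25 + 0.25 − 2ρ·0.25) + (0.25 + 0.24 − 2ρ·√(0.25·0.24))] / 388

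Power = Φ(0.10 / SE − 1.96)

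- ρ = 0 (independent waves): Var = 0.99/388, SE 5.05 points, power 51%; 80% would need 1,729 per arm per wave after the same inflation.
- ρ = 0.3: Var = 0.693/388, SE 4.23 points, power 66%; 1,209 needed.
- ρ = 0.5: Var = 0.495/388, SE 3.57 points, power 80%; 865 needed.
- ρ = 0.7: Var = 0.297/388, SE 2.77 points, power 95%; 520 needed.

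At ρ = 0.5 the DiD variance is almost that of the two-group comparison in step 1, which is why 80% returns there. That value is a consequence of the chosen ρ and does not confirm the plan.

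**4. Dilution, only if the endline were a new, unrestricted draw.** With L listed families in the intervention union councils, the enrolled share is f = 863/L and the expected contrast is 10·f points. L is not given, so a range is shown. Power is for the step 1 endline comparison with 388 effective families per arm and p2 = 0.50 + 0.10·f.

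- L = 1,000: f = 86%, 8.6 points, power about 67%.
- L = 1,500: f = 58%, 5.8 points, 36%.
- L = 2,000: f = 43%, 4.3 points, 22%.
- L = 3,000: f = 29%, 2.9 points, 12%.
- L = 5,000: f = 17%, 1.7 points, 7%.

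**The case against.** The best defence is that the document, read as a whole, already describes a cohort. The survey sentence never says that a new or independent sample is drawn, and it fits one selection interviewed twice. The eligibility text is the more specific rule and limits the endline to enrolled families. One total of 1726 covers both waves, and one identifier runs through all forms. The limitations sentence is loosely written, mixes tenses, and could concern matching of respondents or of arms.

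Most of this stands. A reader might infer that the planned effect will be diluted. The documents do not support that: dilution needs an unrestricted draw that the eligibility text rules out, and even a re-drawn sample confined to enrolled families would not dilute. A reader might also blame the 51% power on the inconsistency. It largely reflects a separate matter, namely that the sample size was set for a two-group comparison and not for a DiD. Nor does the estimator change in a complete two-wave cohort, because the DiD of arm means equals the between-arm difference in mean within-family change. Only the standard error differs.

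The defence does not remove the conflict between the eligibility text and the limitations text, or the open wording of the survey section.

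**Conclusion.** The inconsistency is real and should be settled before endline fieldwork. Follow-up of the enrolled families is the likelier intent, and the text should say so in one way only.

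The consequence that needs no fresh-draw assumption is the DiD standard error. It runs from 5.05 points with independent waves to 2.77 points at ρ = 0.7, with power from 51% to 95% for a 10-point effect. This rests on assumed values of ρ, on the plan's design effect of 2 applying equally to the change, and on a normal approximation.

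Dilution is a conditional risk. It would follow only from carrying out the survey sentence as a new draw without the eligibility restriction, and its size (enrolled share 86% to 17%) rests wholly on assumed list sizes.

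**What to change.** Reconcile the three sections:

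- In Quantitative household surveys, state that random selection from the insurance list happens once, before baseline, and that the same enrolled families in both arms are re-interviewed at endline, linked by the existing unique identifier.
- In Data analysis, define the DiD with a standard error that accounts for the pairing of waves within families.
- In Possible limitations and strengths, revise the sentence on same-sample comparison to agree. If a new endline sample is truly intended, limit its frame to enrolled families and keep that sentence as a limitation.

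The cost is wording, plus tracing effort and some attrition, both of which the eligibility text already implies. The number of planned interviews does not change. The gain is a contrast kept on families who hold the benefit, and a more precise DiD wherever the within-family correlation is positive.

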### Qualitative inquiry

Using exploratory qualitative design, we will conduct interviews/focus groups before and after the intervention. The interviews will be conducted with the target audiences, which include beneficiary families, service providers, health managers/administrators, and policymakers. The overall purpose will be to explore perceptions and attitudes toward insurance schemes. During the baseline quantitative survey (or pre-intervention period), a needs assessment exercise will be conducted using a qualitative approach. The interviews will be aimed at understanding the community’s perceptions of health insurance in general and then specifically on the presently used (inpatient) package and newly designed outpatient package at the PHC level. For example, the following themes will be explored using 5–6 focus group discussions with the intervention beneficiary families:

Utilization – explore the need for these services.Access – explore how you access these services; difficulty in accessing services skilled PHC level healthcare.Affordability – explore the ease of accessing these available services in your area. If you are unable to afford these services, how do you pay or how much can you pay for these services.Existing indoor coverage – explore the benefits and consequences of current benefits and satisfaction.Inputs will be specifically garnered on the design of the package, services covered, mechanism for reimbursement, and frequency of payments.

In addition, in-depth interviews with all service providers will be conducted in the catchment areas to identify the services with the highest perceived utility for end-users and programmatic approaches for price-setting, reimbursement, and payment methods best suited for service providers. Findings will be used to refine and finalize the outpatient services model and undertake detailed financial modeling if required before rollout. Moreover, 6–10 key informant interviews will be conducted with policymakers/insurance experts/program managers (health economists, public health professionals, etc.) with experience implementing health insurance in Pakistan. Input from experts will be used further to inform the final design of the insurance model to explore the utility of adaptive learning. The use of evidence in social health protection initiatives to incorporate outpatient services programming using a benefits package integrated Health Insurance (using capitation payments) and to ascertain progress at the public sector policy-making level concerning project recommendations. At the time of the endline survey (around the post-intervention period), a qualitative stocktaking exercise will be implemented to explain the following themes from beneficiaries’ and service providers’ viewpoints and gauge their experiences:

Experience with the Programme.Impact on the Community.Recommendations for Future Programs.

In addition, we will specifically explore facilitators and barriers encountered by service providers during the intervention period. We will also seek their suggestions to improve the integrated health financing model. The team of researchers, including the principal and co-investigators, will develop the interview guides for beneficiary focus group discussions, service provider in-depth interviews and key-informant interviews during the project inception period by the researcher.

#### Data collection and management

Baseline and endline surveys, including qualitative inquiry, will be conducted by a 3rd party consultant/organization. Enumerators with prior experience will be hired and trained on theoretical and practical aspects of the health insurance programs, study instruments, research ethics, and interviewing techniques. The field supervisor will conduct shadow interviews (observation of data collection) and independent re-interview/assessment of study participants (10% of participants). All data will be collected electronically on tablets. The software applications will have built-in validation checks to minimize data errors. All software applications will be tested before their use in the study. The implementing partners will undertake routine service delivery statistics, clinical monitoring of the quality of care, and client satisfaction.

#### Data analysis

The quantitative data analysis will focus on the combined effect of the complete package of interventions and the outcome(s) rather than exploring each component. Quantitative data will be analyzed through SPSS Software using descriptive and inferential statistics. The main outcome variables will be increased access, uptake, satisfaction, contraceptive prevalence, and reduction in OOP expenditure. Difference-in-differences (DiD) estimation will compare key outcome variables between the intervention and control group pre- and post-intervention (51). It will also measure the intervention effect on any subgroups in the intervention/control groups by comparing key outcome variables between beneficiaries in the intervention and control groups.

For the qualitative data, content and thematic analysis will be done in Nvivo Software version 11. Codes will be developed after reading the transcripts without losing the context. For qualitative analyses, transcripts will be read several times to understand the respondents’ in-depth experiences and views. ‘Meaning units’ that mirror statements will be identified as per the topic guide by highlighting phrases in the transcripts, which will be ‘condensed’, and after that ‘, codes’ will be identified from the ‘condensed meaning units’ without losing the context. Finally, the research team will review the codes independently and group similar codes into sub-categories and categories. From the categories, themes and sub-themes will be identified after systematically analyzing the commonalities, variations, and disagreements. We will further analyse data with a focus on the description and interpretation of message meaning and concepts to validate the study’s findings. Quantitative and qualitative data will be triangulated to provide comprehensive information about the impact of the research intervention. Figure 3 describes the components of the data synthesis plan envisaged for the project.

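### The sizing allows for clustering (design effect 2), but the stated difference-in-differences analysis names no method that carries it into the standard errors

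*Protocol article*

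**What the plan says.** Under Study population and sample size, a two-arm comparison of proportions gives 388 families per arm, and then: "The estimated sample was adjusted for a design effect 2 to account for facility-level clustering and 10% missing data / non-response". The result is 863 per arm. Under Study area, the arm follows the UC, and four UCs take part. Possible limitations and strengths adds that the facilities are chosen by convenience.

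Under Data analysis, "Quantitative data will be analyzed through SPSS Software using descriptive and inferential statistics", and "Difference-in-differences (DiD) estimation will compare key outcome variables between the intervention and control group pre- and post-intervention". No facility or UC term, clustered variance, random effect or survey-design adjustment is mentioned. Possible limitations and strengths lists measures to protect validity (DiD, covariate balance checks, matching or weighting), and clustering is not among them. The Abstract and that same section instead present random selection of families as a safeguard.

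Whether the same families are interviewed twice is unclear. Inclusion and exclusion criteria limits the endline to enrolled beneficiaries. Quantitative household surveys has participants for both rounds drawn at random from the programme list. Possible limitations and strengths speaks of a matched pre-post design as a stronger option that was not taken.

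**The concern.** The plan accepts that families sharing a facility are correlated enough to double the variance, and it delivers treatment by cluster. A design effect in the sizing is only half of what that requires, because the analysis must use a standard error that contains the same inflation. Drawing families at random within a UC does not help: every family in that UC still shares its arm, its local providers and any local change over the year.

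If the analysis were run with ordinary family-level standard errors, its intervals would contradict the variance assumption used to justify 863 per arm. One stated objective is evidence for scale-up, so intervals that are too narrow could let chance differences between a few localities pass for programme effects.

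**Working it through.** **Inputs from the article** (Study population and sample size, except the last)
- Baseline: "assuming the overall prevalence of health outcomes to be 50% (conventional) at baseline".
- Effect: "an anticipated 10-percentage point change because of the intervention", so 50% against 60%.
- Error rates and result: "with 80% power and 0.05 significance level, the total estimated sample was 388 for each study arm". Sidedness is not stated; two-sided reproduces the figure.
- Design effect 2 at facility level; 10% loss.
- Four UCs, arms assigned by UC (Study area).

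**Step 1. Reproduce the sizing.** The two-sided two-proportion formula without continuity correction gives 388 per arm. Then 388 × 2 = 776, and 776 / 0.90 = 862.2, rounded up to 863. Both figures reproduce, so the design effect was applied in full to a single contrast between arms.

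**Step 2. Single-wave comparison with clustering ignored.** The naive standard error is 1/√2 = 0.71 of the true one.

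Type I error = 2 × [1 − Φ(1.96/√DE)]. With DE = 2: 1.96/1.414 = 1.386, giving 0.1658. Coverage of a nominal 95% interval is 1 − 0.166, about 83%.

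**Step 3. Carry this to the DiD.** Stable facility differences cancel in a before-after contrast. Let r be the correlation of facility effects between waves, m the families per facility and ρ the intracluster correlation. Assumptions, since the article gives none of these: five facilities per arm, so m = 863/5 = 172.6, and ρ = 1/(m − 1) = 0.0058, which makes the single-wave design effect 2. The number of facilities matters little, because mρ = m/(m − 1) is close to 1 for any large m.

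*Repeated cross-sections:* DE = 1 − ρ + mρ(1 − r).

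*Same families, analysed as pairs,* with family-level correlation s (assumed 0.3 to 0.5): true variance over naive paired variance = [(1 − ρ)(1 − s) + mρ(1 − r)] / [(1 − ρ)(1 − s) + ρ(1 − r)].

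| r | Cross-sections: DE | Type I error | Paired, s = 0.3: ratio | Type I error | Paired, s = 0.5: ratio | Type I error |
|---|---|---|---|---|---|---|
| 0 | 2.00 | 16.6% | 2.43 | 20.8% | 2.99 | 25.7% |
| 0.5 | 1.50 | 10.9% | 1.72 | 13.5% | 2.00 | 16.6% |
| 0.8 | 1.20 | 7.3% | 1.29 | 8.4% | 1.40 | 9.8% |
| 1 | 0.99 | 4.9% | 1.00 | 5.0% | 1.00 | 5.0% |

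**Step 4. Same families, link ignored.** The naive variance then omits a positive within-family covariance that lowers the true variance. At r = 0 the ratio falls from 2.00 to 1.70 (s = 0.3) or 1.50 (s = 0.5), and the error rate to 13.3% or 11.0%. At r = 0.8 and s = 0.3 it is 3.9%, below nominal. Ignoring the link therefore widens intervals.

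**Step 5. Clustering at UC level.** Assume two UCs per arm, evenly filled: m = 863/2 = 431.5. For a single wave, DE = 1 + 430.5 × ICC. An ICC of 0.0023 gives DE = 2 (about 17%); an assumed ICC of 0.01 gives DE = 5.3 (39%). A DiD on UC-period means has four UC-level changes and two arm means, so 4 − 2 = 2 degrees of freedom and a critical t of about 4.3 rather than 1.96.

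**The case against.** The strongest reply is that silence is not a commitment. The sentence on software and inferential statistics is generic and excludes nothing. The variance method is often left to a statistical analysis plan, and a condensed article need not give it. The authors plainly know about the clustering. Under Ethics and dissemination, each participant's identifier is built partly on the allocated facility, so the variable needed for a clustered analysis should be available.

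Much of this stands. A reader might infer that the plan will analyse families as independent, so that its tests would have a 17% false-positive rate. The article does not support that. It states no standard-error method, and 16.6% belongs to a single-wave contrast, which is not the named estimator. Nor does the missing link between a family's two interviews add to the problem; step 4 shows that it usually works the other way.

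What the reply does not remove is the mismatch inside the article. Clustering is the one source of dependence that the plan quantified, yet it is absent both from the analysis and from the list of techniques meant to protect validity, while random selection of families is put forward as reassurance.

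**Conclusion.** The point holds as an inconsistency between the sizing and the stated analysis. If clustering is ignored, a nominal 5% single-wave comparison has 16.6% type I error and about 83% coverage under the plan's own design effect. That result needs no outside input.

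For the DiD no single rate can be given. Under the assumptions in step 3 it runs from about 5% to 17% for repeated cross-sections and from 5% to 26% for families analysed as pairs, depending on the unstated between-wave correlation. UC-level clustering could push it higher: step 5 reaches 39% at an assumed ICC of 0.01, again for a single wave. These ranges show what is at stake; they do not predict the trial's error rate. The cluster level and variance method should be fixed before the endline data are seen.

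**What to change.** In Data analysis, state the following:
- The effect is the arm-by-period interaction.
- Its variance accounts for clustering at least at facility level, the level used in the sizing, with a small-sample correction for few clusters.
- A family term is included only if the same families are re-interviewed. Inclusion and exclusion criteria, Quantitative household surveys, and Possible limitations and strengths must first be reconciled on this.
- A DiD on UC-period means is reported as a sensitivity check.

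Under Possible limitations and strengths, add that assignment by four UCs leaves about 2 degrees of freedom at that level, and that facility-level adjustment does not remove variation between UCs.

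The cost is some rewording, slightly more analysis work and wider intervals. At UC level the loss of precision is marked (critical t of about 4.3), so that check may be inconclusive. The sample size is unchanged by this point.
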